### Study procedures

#### Recruitment and consent

Participants are recruited from 11 acute stroke units or rehabilitation units in university hospitals and other local hospitals providing acute care in Norway. Participants are identified by specifically trained clinical staff in the participating units, based on the stated inclusion and exclusion criteria following the recruitment protocol of the study. Recruitment occurs when the patient is medically stable and considered ready for receiving information about the study. Eligible patients, who have suffered an acute stroke within the last four weeks, will receive oral and written information and be invited to enter the study. Potential participants who are not ready to decide whether they will participate or not at this early stage, will be given information and asked if they can be contacted at a later stage. The written information sheet and consent form have been developed to accommodate aphasia and have been approved by the Regional Medical Ethics committee and the Data Protection Officer at the participating hospitals. Recruitment will occur over a three-year period.

#### Randomization and blinding

A computer-generated block randomization procedure created by a statistician independent of the research group is applied. The participants are randomized in blocks of 10 to minimize allocation bias, and to ensure an equal group size in intervention and control groups. The randomization is stratified by study center. Opaque randomization envelopes with a five-digit patient identification number printed outside and a note specifying intervention or control inside, are prepared according to the computer-generated randomization lists by an assistant independent of the research group. Two regional study coordinators carry out the randomization process following a completed baseline assessment. To ensure blinding of the assessors, group allocation is communicated solely to the patient him or herself and the health care professional delivering the intervention when the patient is randomized to the intervention group. To maintain blinding at follow up assessments, a text message is sent from the study coordinator to each participant prior to each assessment reminding them not to reveal their group allocation to the assessor.

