### Control group

The control group receives treatment as usual and no intervention beyond participation in the assessment interviews at 1, 6, and 12 months. As participants are recruited from a variety of settings (acute stroke care and rehabilitation units), we anticipate some variation in the usual care provided. Provision of rehabilitation services is the responsibility of the community health care services in Norway, and this adds to the anticipated variability in services. Systematic psychosocial rehabilitation and support is not implemented in community health care services in Norway. However, adoption of the National stroke treatment guidelines in the acute phase of stroke (based on international stroke treatment guidelines) is high in Norway. To control for the potential variability in “usual care”, we collect data on the types of rehabilitation services received in both arms of the study.

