### Statistical analysis

Data analysis will be conducted as intention-to-treat. Missing data will be imputed using multiple imputation technique [71]. All analyses will be performed using statistical software such as IBM SPSS or R. For group comparisons of individual variables, categorical variables will be analyzed using chi-squared tests, and continuous variables will be analyzed using t-tests or Mann-Whitney U tests (for two-group comparisons) and F-tests or Kruskal-Wallis tests (for more than 2 groups). The primary statistical analysis will be a repeated measures logistic regression model for the dichotomized output variable “normal mood yes/no” (GHQ-28 < 5 versus GHQ-28 ≥ 5) with two measurements for each patient (i.e. one at 6 months and one at 12 months), with one binary input variable specifying group allocation. Independent variables will include demographic variables, stroke type and severity measurements, rehabilitation service use and relevant medical variables. Medical and demographic variables will be included in the data analysis model to control for group differences at baseline. Secondary analyses, e.g. sub-group analyses, will be conducted with primary, secondary and process outcomes. The psychometric properties of GHQ-28 will be examined to confirm stability of dimensions in a Norwegian general stroke population across time points. All statistical tests will be performed as two-sided tests with a significance level of 0.05.

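### Randomisation is stratified by study centre, but the primary model does not name centre; if centres differ in outcome, the test is conservative and some power is lost

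*Protocol article*

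**What the plan says.** Under Randomization and blinding the article states "The randomization is stratified by study center" and "The participants are randomized in blocks of 10 to minimize allocation bias". Centre is the only stratification factor named. Recruitment and consent gives the number of sites: "Participants are recruited from 11 acute stroke units or rehabilitation units".

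Statistical analysis sets out the primary model in some detail. It is a repeated measures logistic regression for normal mood (GHQ-28 below 5) at 6 and 12 months, "with one binary input variable specifying group allocation". On covariates it says "Independent variables will include demographic variables, stroke type and severity measurements, rehabilitation service use and relevant medical variables", and it gives the reason: "Medical and demographic variables will be included in the data analysis model to control for group differences at baseline". Centre is not mentioned there, nor in the model under Sample size calculations. The test level is also set: "All statistical tests will be performed as two-sided tests with a significance level of 0.05".

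The Control group section says "we anticipate some variation in the usual care provided", because participants come from different kinds of unit and community services differ. The Discussion repeats that acute and rehabilitation services vary.

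**The concern.** Stratifying by centre forces the arms to be nearly balanced within each centre. If centre predicts outcome, this removes the between-centre part of the chance difference between arms, so the treatment estimate varies less from trial to trial than under simple randomisation. A model without centre does not know this. It reports a standard error that includes the between-centre part, and its p-values and confidence intervals are then wider than the design warrants.

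The article expects care to differ between settings, so a centre effect is plausible here. It fixes the model type, outcome cut-off, visits, group term and covariate classes, and none of those classes naturally covers study centre. An analyst who followed the text as written would leave the stratification factor out. What is at stake is efficiency and the match between analysis and design.

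**Working it through.** **The plan's own figure.** Sample size calculations gives 300 patients (150 per arm) for an odds ratio of 1.6 and 80% power with two measurements each. It states neither the control rate nor the within-patient correlation ρ, so 300 cannot be reproduced from the article alone. With n per arm = n(single measurement) × (1+ρ)/2, a control rate of 0.35 and ρ = 0 give 297 × 0.5 = 148.5, or 149. Control rates of 0.40 to 0.50 with ρ = 0.05 give 151 to 153. The stated size is therefore reachable with ρ near 0. None of this involves centre.

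**Inputs to the check.**
- From the article: 300 patients, 1:1 allocation, two visits, odds ratio 1.6, blocks of 10 within centre, 11 units, two-sided 0.05.
- Assumed: each unit is one stratum and all are of equal size (300/11, about 27 patients); ρ is 0 or 0.5; the between-centre intraclass correlation (ICC) on the latent logistic scale runs from 0 to 0.20.
- The standard error with no centre effect and ρ = 0 is 0.164, which matches a control rate near 0.45: √(2/(300 × 0.45 × 0.55)) = 0.164.
- Not modelled: the other covariates that the article plans.

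**Method.** 2,500 simulated trials per scenario. The logistic model used patient-level robust standard errors and was fitted to the same data without and with centre as a fixed effect. As an anchor, with no centre effect and ρ = 0 the simulated power without centre is 82.3%, against 81.9% from the formula at a control rate of 0.45.

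| ρ | ICC | Type I error, without / with centre | Model SE ÷ true SD, without centre | Power %, without → with | Gain, points |
|---|---|---|---|---|---|
| 0 | 0 | 0.051 / 0.056 | 0.99 | 82.3 → 83.1 | 0.8 |
| 0 | 0.02 | 0.045 / 0.054 | 1.01 | 80.8 → 81.9 | 1.1 |
| 0 | 0.05 | 0.048 / 0.060 | 1.01 | 77.6 → 80.4 | 2.8 |
| 0 | 0.10 | 0.030 / 0.044 | 1.07 | 72.7 → 78.6 | 5.9 |
| 0 | 0.20 | 0.025 / 0.053 | 1.11 | 63.8 → 74.3 | 10.5 |
| 0.5 | 0 | 0.054 / 0.057 | 0.99 | 66.8 → 67.9 | 1.1 |
| 0.5 | 0.02 | 0.050 / 0.056 | 1.02 | 62.2 → 64.4 | 2.2 |
| 0.5 | 0.05 | 0.043 / 0.052 | 1.04 | 61.6 → 64.6 | 3.0 |
| 0.5 | 0.10 | 0.034 / 0.044 | 1.05 | 58.2 → 63.1 | 4.9 |
| 0.5 | 0.20 | 0.034 / 0.057 | 1.09 | 48.6 → 58.8 | 10.2 |

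Type I error comes from runs with odds ratio 1; the ratio and power come from runs with odds ratio 1.6. Monte Carlo error on each power figure is about 0.8 to 1.0 point.

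**Where the gain comes from.** Take ICC 0.10, ρ = 0, and use power ≈ Φ((estimate − 1.96 × SE)/true SD).
- Without centre: (0.435 − 1.96 × 0.171)/0.160 = 0.62, power about 73%.
- With centre: (0.475 − 1.96 × 0.172)/0.174 = 0.79, power about 79%.

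The reported standard error hardly moves (0.171 to 0.172). At ICC 0.20 with ρ = 0.5 it rises, from 0.207 to 0.222. What changes is the log odds ratio: without centre it is attenuated (0.435, against ln 1.6 = 0.470), and with centre it moves to the larger value conditional on centre. The unadjusted standard error is too large only against its own sampling SD (0.171 against 0.160).

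**Second simulation.** A separate run with 11 × 28 = 308 patients, and the centre effect given as an SD on the log-odds scale, points the same way. ICC = SD²/(SD² + 3.29), so SD 0.5 is 0.25/3.54 = 0.07 and SD 0.8 is 0.64/3.93 = 0.16. Type I error without / with centre was 0.036 / 0.046 and 0.032 / 0.048, and power went from 59.0% to 62.1% and from 54% to 61%. At SD 0.3, type I error was 0.047 / 0.052, close to nominal. With no centre effect, power was 63% against 65%, so about 2 points are not a real gain.

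**The case against.** The strongest reply is that a condensed article commonly leaves exact model terms to the analysis plan, which is not shown. That stands in part. A reader might infer that the plan excludes centre, but the covariate list is by category and not closed, so only the statement that centre is not named is supportable. The point survives because the article goes further than a general reference to adjustment: it specifies the model and gives baseline imbalance, not the design, as the reason for covariates.

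A second reply is that the article already deals with variation in care. The Control group section says that rehabilitation services received are recorded for this purpose, and service use is in the model. This also has weight. Service use, severity and demographics (Table 1 includes urban or rural residence) could absorb part of the centre differences, and the simulations omit them, so the losses shown are not those of the full planned model. Service use is not a full substitute, however: Tables 1 and 2 show it recorded after randomisation as well as at baseline, so it may be affected by allocation. Centre is fixed beforehand.

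Third, the effect is conditional and small. That is correct, and the verdict is worded accordingly.

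**Conclusion.** The concern holds in a limited form. The only stratification factor is not named in the primary model. If centres differ in outcome, a model without centre is conservative and loses some power. The loss is negligible up to an ICC of about 0.02, about 3 points at 0.05 and 5 to 6 points at 0.10, and 1 to 2 points of each figure are noise or a slightly liberal adjusted test (type I error 0.044 to 0.060 with centre). These figures rest on assumed ICCs, equal centres, ρ of 0 or 0.5, and no other covariates.

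Three stronger readings are not supported. Omitting centre does not inflate type I error; without centre it stays near 0.05 or falls below it. Adding centre does not shrink the logistic standard error; the gain comes with a larger, conditional odds ratio. Nor do the documents show that power is already below 80%: that depends on the unstated within-patient correlation (150 per arm gives about 61 to 65% at ρ = 0.5, and about 80% near ρ = 0) and is a separate question.

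**What to change.** In Statistical analysis, name study centre, as used in the randomisation, in the primary and secondary outcome models. Use a fixed effect, or a random intercept if some centres recruit few patients. State that the resulting odds ratio is conditional on centre, so that it is not read as the marginal one.

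The cost is one model term and a slightly different target odds ratio. If centres do not differ, the simulations show no visible loss of power. Trial status reports data collection as still running when the article was submitted, so at that point the term could still be specified before the analysis.

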### The intervention: Promoting psychosocial well-being following stroke

#### Theoretical perspectives underpinning the intervention

The overall goal of the intervention is to promote psychosocical well-being, defined as: (a) a basic mood of contentment, pleasure and well-being and the absence of sadness or a feeling of emptiness, (b) participation and engagement in meaningful activities beyond oneself, (c) good social relations and a feeling of loving and being loved in mutual relation(s), and (d) a self-concept characterized by self-esteem, self-acceptance, usefulness and belief in one’s own abilities [42]. Each of these dimensions will be addressed in the dialogues.

Experiences of chaos and a lack of control are major threats to well-being following stroke. Antonovsky’s theory connects health and well-being to the experience of a sense of coherence in life (SOC). SOC is promoted by experiencing life events as comprehensible (cognitive), manageable (instrumental/behavioural) and meaningful (motivational) [43, 45, 46]. SOC is seen as an essential intermediate goal for promoting psychosocial well-being [37].

To promote SOC, we draw on narrative theory [47, 48], which emphasises that human beings create meaning in their lives through the stories they tell. Through stories, people seek to negotiate a position within a given social context that gives meaning, direction, identity and value to their lives [49, 50]. Research suggests that telling one’s story is a fundamental need following a traumatic event and that this may promote well-being in and of itself [51, 52]. We assume that being encouraged and supported to tell one’s story, receiving response from others and experiencing that stories are shared would stimulate reflection and adjustment and strengthen identity, self-understanding and self-esteem.

People suffering from aphasia are restricted in their natural abilities to tell their stories [53, 54]. The method “Supported Conversation for Adults with Aphasia” assigns a particular responsibility for facilitating social interactions to the person without communication difficulties and provides a number of different techniques that may enhance communication and understanding in dialogues with PWA [55].

To promote coping and development of new life skills, we apply ideas from guided self-determination [56], an approach inspired by empowerment philosophy. It highlights the importance of being in control of one’s own recovery- and adjustment process. In this approach, the role of the health care professional is conceptualized as being a “supporter” or “coach” rather than a “carer” or “therapist”. The participants are in charge of the dialogues in the sense that they decide what to focus on in each encounter, whereas the health care professional follows the participants’ lead. At the same time, the structure of the intervention, with the guiding topical outline of each encounter and supporting work sheets, provide a framework for the dialogues that the participant and health care professional may follow or deviate from [37].

### The intervention

The intervention consists of 8 one to one and a half hour dialogue-based sessions between the stroke survivor and a specially trained health professional (RN or OT). Each meeting has a guiding topical outline, which addresses significant issues described in the research literature (e.g. bodily changes, emotional challenges, personal relations, daily life issues, meaningful activities, existential issues, important values etc.) (Fig. 1).

**Fig. 1 Fig1:**
[figure not shown]
Flowchart of intervention with main content in each session

In the sessions, work sheets developed to support the dialogues are used. The work sheets consist of drawings, figures, unfinished sentences, and key words that point to the topic that the participants are invited to address. The work sheets are adapted to persons with aphasia. The sessions are in part carried out as open dialogues, where the participants are invited to tell about issues that are important to them at the time, and in part structured by the work sheets developed for the particular meeting. If the participant initially introduces a topic that is different from the topic suggested for the particular session, the health care professional changes the planned order of topics, i.e. by using work sheets from other planned sessions. In this way, the intervention is made flexible to meet the individual participant’s needs. The first session occurs approximately between 4 and 8 weeks post stroke, the last is conducted before the 6 months post-stroke time point (Fig. 1). The intervention is offered to the participants during the period when the recovery- and adjustment process is assumed to be most challenging. The sessions take place at times of increased vulnerability due to known transition points (i.e. at discharge, when physical improvement slows down, when people tend to assume new challenging roles or activities etc.). The number of sessions (8) is chosen in an attempt to balance the ideal with the realistic (i.e. as few encounters as possible but enough to provide adequate support).

### Control group

The control group receives treatment as usual and no intervention beyond participation in the assessment interviews at 1, 6, and 12 months. As participants are recruited from a variety of settings (acute stroke care and rehabilitation units), we anticipate some variation in the usual care provided. Provision of rehabilitation services is the responsibility of the community health care services in Norway, and this adds to the anticipated variability in services. Systematic psychosocial rehabilitation and support is not implemented in community health care services in Norway. However, adoption of the National stroke treatment guidelines in the acute phase of stroke (based on international stroke treatment guidelines) is high in Norway. To control for the potential variability in “usual care”, we collect data on the types of rehabilitation services received in both arms of the study.

### Outcome measurements

The primary outcome is psychosocial well-being as measured by The General Health Questionnaire (GHQ-28). The GHQ was developed by Goldberg [57] and has been translated into Norwegian by Malt and colleagues [58]. The GHQ-28 has been used in other trials involving psychosocial stroke interventions [31, 32, 59] and was also used in Hilari et al.’s study of SAQOL-39 [44], which will facilitate comparison.

The Stroke Aphasia Quality of Life scale (SAQOL-39) addresses general dimensions of health-related quality of life (HRQOL). It is based on the Stroke-specific Quality of Life scale (SS-QOL) and was adjusted for persons with aphasia. It has been found to be valid and reliable in the general stroke population and to be sensitive to change [44, 60]. SAQOL 39 was tested in the exploratory trial for appropriateness and was found to function adequately.

Sense of Coherence (SOC-13), has been translated into Norwegian and previously been applied in studies focusing on psychosocial well-being [61–64].

NIHSS is a well-established assessment for measuring stroke severity used in numerous stroke studies [65].

Yale is a one item instrument measuring the presence or absence of depression as experienced by the person. It has been validated as a measurement for depression in stroke patients [66, 67].

Lee Fatigue Severity Scale (5 items) and Fatigue Questionnaire (2 items) have been chosen to measure fatigue in this study [68, 69].

The Ullevaal Aphasia Screening test (UAS) is a quick and simple aphasia screening which can be used by health professionals other than speech therapists to discriminate between aphasia and normal language. It has been shown to be reliable in several studies [41, 70]. The instruments and related constructs are summarized in Table 1.

**Table 1 Tab1:** Overview of instruments and related constructs

Construct	Instrument	Domains
Psychosocial well-being	The General Health Questionnaire-28 (GHQ-28)	28 item general scale measuring emotional distress. Four subscales (somatic symptoms, anxiety/insomnia, social dysfunction and serious depression
Psychosocial well-being	The Stroke and Aphasia Quality of Life scale (SAQOL-39)	Disease-specific quality of life scale, measures patient’s perspective of stroke’s impact on ‘physical’, ‘psychosocial’ and ‘communication’ domains.
Sense of coherence	Sense of Coherence scale (SOC-13)	Self-report questionnaire, 13 components, measuring the main concepts in the SOC theory; coherence, meaningfulness and manageability. 13 items scored on a Likert scale, ranging from 1 to 7. Higher scores indicate a stronger SOC.
Depression and anxiety	The Yale Brown single item questionnaire (Yale)	One yes/ no question
Fatigue	Lee’s Fatigue scale-5 (Lee-5)	A 0–10 scale assessing symptoms of fatigue
Fatigue	Fatigue Questionnaire-2 (FQ-2)	One yes/ no question, If yes; length of symptoms.
Demographics		Age, gender, ethnic background, education, type of work/studies, marital status, living condition, family/network, place of living (urban/rural)
Medical information		Time of stroke, type / localization of stroke, type of medical treatment after stroke, medication, other chronic diseases, earlier depression / mental disorders, rehabilitation services provided, type and amount of health care/practice assistance provided in the community.
Stroke severity	National Institutes of Health Stroke Scale (NIHSS)	A questionnaire used by healthcare providers to objectively quantify the impairment caused by a stroke.
Aphasia	The Ullevaal Aphasia Screening Test (UAS)	Screening for aphasia.

All instruments will be administered at T1 (at 1 month post-stroke and before randomization and potential initiation of the intervention), at T2 (6 months after stroke, approximately two weeks after the end of the intervention), and at T3 (12 months after stroke / 6 months after the end of the intervention). The instruments will be administered by data collectors with a health care background (RN and OT) using a personal interview format. The assessor is blinded to group allocation at each data collection point. At T0 (at hospital / rehabilitation unit) medical information about the stroke and stroke severity (NIHSS-score) will be collected. Data and all appropriate documentation will be stored for a minimum of 5 years after the completion of the trial, including the follow-up period. The Standard Protocol Items: Recommendations for Interventional Trials (SPIRIT) Flow diagram showing the schedule for enrolment, interventions and assessments is provided in Table 2.

**Table 2 Tab2:** Schedule of enrolment, intervention, and assessments (SPIRIT)

Time point	Enrolment -t1 4–8 weeks post-stroke	Data collection t1 at time of enrolment	Allocation Immediately following data collection t1	Intervention period 4 weeks-6 months post-stroke	Data collection t2 6 months post-stroke	Data collection t3 12 months post-stroke
Enrolment						
Eligibility screen	X					
Informed consent	X					
Intervention						
Randomization			X			
Intervention: Psychosocial dialogues				X		
Control: Usual care				X		
Assessments						
Primary outcome:						
GHQ 28		X			X	X
Secondary outcomes:						
SAQOL 39		X			X	X
SOC 13		X			X	X
Yale		X			X	X
Characteristics of sample:						
Demographics		X			X	X
Lee 5		X			X	X
FQ 2		X			X	X
Medical information	X	X			X	X
NIHSS	X					
UAS		X				

